## 7.2. Primary and secondary analyses

We will use cluster specific methods because communities rather than individuals (participants) are randomized and the data are to be collected at the individual level. For primary analysis, we will compare the nine intervention clusters to the three control clusters for the primary outcome of engagement in regular aerobic, flexibility, and/or muscle-strengthening activities at one-year follow-up using a generalized linear mixed model (GLMM) with sex, age, BMI,

self-rated health, years of education, employment status, engagement in farming, chronic low back and knee pain, chronic disease history, category of population density of each cluster, engagement in regular aerobic, flexibility, and/or muscle-strengthening activities at baseline, and group allocation (i.e., intervention or control) as fixed effects and community (cluster) where respondents live as a random effect.

As secondary analyses, we will compare the nine intervention clusters to the three control clusters to determine changes in VAS pain scores and chronic pain of low back and knee using a GLMM, adjusted for sex, age, BMI, self-rated health, years of education, employment status, engagement in farming, engagement in regular physical activity at baseline, chronic disease history, and category of population density. In addition to the comparison between all intervention groups and the control group, we will compare each intervention group (i.e., Group A, FM, and AFM) to the control group for primary and secondary outcomes and changes in engagement in each different activity (i.e., aerobic, flexibility, and muscle-strengthening activities) in the same manner using a GLMM.

As exploratory analyses, subgroup analyses will be conducted to detect significant differences in intervention effect, after stratification by sex, age group (40–59 and 60–79), and the market segment (primary communication target segment and the remaining population). Associations for engaging in physical activity, low back and knee pain (VAS scores and chronic pain), awareness of the campaign, and other obtained variables will also be analyzed as exploratory analyses.

We will assign cluster specific mean values to missing values. Significance will be set at  $P < 0.05$ . Analyses will be carried out using SAS version 9.1.3 and SPSS 14.0J.

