## 5. Population-based evaluation

The effectiveness of the intervention will be evaluated using a population-based survey, which will be a prospective cohort design. As a baseline survey, self-administered questionnaires will be mailed to random participants, i.e., those who are randomly sampled using a computer-based resident registry system. Eligible participants will be all men and women aged 40 to 79 years living in the study areas (i.e., 12 communities). Those excluded are individuals in assisted living facilities, those who require long-term care, or those who cannot complete the questionnaires by themselves due to disability. We considered systematically reviewed effective methods to increase response rates,[39] and decided to incorporate the following recommended techniques, i.e., non-monetary incentives, university sponsorship, personalized and relatively short questionnaires, and assurance of confidentiality. We will also send postcard reminders to non-responders, add a preface from the Vice-Mayor to the front cover, make announcements by local audio broadcast and local cablecast, establish a call center for questions, and send a written request for cooperation to community leaders.

Both a one-year and three-year follow-up questionnaire survey from the conducting of the baseline survey is planned (Fig. 1). Follow-up questionnaires will be mailed to the respondents in the baseline survey. Surveys for mortality, functional independence (requirement of long-term care), and morbidity of specific diseases in successive years are also planned as future exploratory studies.

All respondents will give written informed consent to participate in these cohort surveys at the baseline survey. The content of the questionnaires will be the same for all residents. Both participants and data collectors will be randomly-sampled residents. Residents will be blinded to (not informed about) the study design and hypothesis (i.e., the existence of the control group and cluster allocation).[40] While the implementing staff of the CWC (intervention providers) and data analysts will not be blinded to the cluster allocation, the CWC collaborators (e.g., staff of each community's self-administered organization, Senior Citizens' Clubs, schools and clinics) will be blinded to (not informed about) the study design and hypothesis (the existence of the control group and allocations of other study communities). The Mayor, Vice-Mayor,

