### *6.2. Secondary outcomes*

Low back and knee pain are to be evaluated as secondary outcomes. A visual analogue scale (VAS) from 0 mm (no pain) to 100 mm (most intense pain) will be used to assess pain intensity.[41] Additionally, chronic musculoskeletal pain is to be defined as current pain (i.e., an episode of pain during completion of the questionnaire) lasting longer than 3 months within the past 12 months.[42]

We will also evaluate awareness of the campaign for exploratory analysis. Awareness is to be evaluated based on a respondent's encounter with the following CWC components: (1) posters, leaflets, and banners, (2) local audio broadcasts, (3) mass - and individual- encouragement by health professionals during community-based medical check-ups and at community events, (4) individual encouragement by family, friends, and/or neighbors, (5) advice from physicians and medical staff in medical institutions.

Sociodemographic variables will include sex, age, body mass index (BMI) calculated from self-reported weight and height in  $\text{kg/m}^2$ , self-rated health (excellent; good; fair; poor), years of education, employment status (yes or no), and engagement in farming (yes or no). Most of these variables were considered to be related to physical activity.[43–46] Other information, including overall moderate to vigorous physical activity measured by the short version of the International Physical Activity Questionnaire,[47, 48] pain management, falls, psychological distress,[49] chronic disease history (e.g., heart disease, stroke, diabetes), and general health habits (e.g., smoking, drinking, participation in health education classes) will also be evaluated. Based on the information obtained by the questionnaire, those unable to walk unaided will be excluded from the analyses.

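### The secondary pain models name baseline physical activity but not the baseline value of the pain outcome itself, which costs precision and leaves chance imbalance in the VAS estimate

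*Protocol*

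**What the plan says.** Section 7.2 describes the secondary analyses as a comparison of "changes in VAS pain scores and chronic pain of low back and knee using a GLMM, adjusted for sex, age, BMI, self-rated health". The list goes on with education, employment and farming and ends with "engagement in regular physical activity at baseline, chronic disease history, and category of population density". That makes ten covariates. Baseline physical activity is among them; baseline VAS and baseline chronic pain are not.

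The primary model in the same section is built differently. It carries its own baseline, since the list of terms ends with "muscle-strengthening activities at baseline, and group allocation (i.e., intervention or control) as fixed effects". It also includes pain as a covariate: "chronic low back and knee pain, chronic disease history, category of population density of each cluster".

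The section then extends the approach to comparisons of each single campaign with control, and to "changes in engagement in each different activity", without saying which baseline term goes into those models.

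Baseline pain is available. Section 5 states: "As a baseline survey, self-administered questionnaires will be mailed to random participants". The follow-up questionnaires go to those who answered at baseline, so each person followed up also has a baseline questionnaire. Section 6.2 defines the measure: "A visual analogue scale (VAS) from 0 mm (no pain) to 100 mm (most intense pain) will be used to assess pain intensity". The questionnaire in section 12 has duration, current-pain and VAS items for the low back (items 29 and 31) and the knee (items 35 and 37).

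**The concern.** For an outcome measured before and after, its own baseline value is usually the strongest single predictor of follow-up. The protocol follows this for the primary outcome. For pain, the chronic-pain covariate drops out when pain becomes the outcome, and no baseline pain term takes its place.

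Two things are at stake. One is precision. The other is the effect of chance imbalance. Only three communities serve as control, and section 3 stratifies the randomisation on population density alone, so mean baseline pain can differ between arms. Low back and knee pain are the named secondary outcomes, and the campaign's key message (section 4.1) is about them, so these estimates will be read closely.

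**Working it through.** **The plan's own figures.** The protocol gives no sample size, correlation, SD or ICC for pain, so there is no pain figure to reproduce. Section 7.1 supplies the cluster size (250), the clusters (nine and three) and an activity ICC of 0.00174. Its primary calculation reproduces: the printed formula with 58% and 66% gives 511.6, hence 512 control and 1,536 intervention. The design effect is 1 + 249 × 0.00174 = 1.433 (stated 1.44).

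**VAS, precision.** Let s be the SD of VAS, equal at both times, and r the correlation between baseline and one year.
- Change score: variance 2(1-r)s².
- Baseline VAS as covariate: variance (1-r²)s².
- Ratio: 2(1-r)/(1-r²) = 2/(1+r).

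| assumed r | variance ratio | SE ratio | shift per 1 mm baseline difference |
|---|---|---|---|
| 0.4 | 1.43 | 1.20 | -0.6 mm |
| 0.5 | 1.33 | 1.15 | -0.5 mm |
| 0.6 | 1.25 | 1.12 | -0.4 mm |
| 0.7 | 1.18 | 1.08 | -0.3 mm |

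**VAS, imbalance.** If the intervention arm starts d mm higher by chance, the expected follow-up difference with no campaign effect is r·d. The change contrast is then r·d - d = -(1-r)d. With baseline VAS in the model the shift is zero.

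**Simulation.** In 3,000 runs with nine against three clusters of 250, ICC 0.00174 and the same r between and within clusters, the variance ratio was 1.33 at r = 0.5 and 1.18 at r = 0.7. The slopes of the change estimate on baseline difference were -0.50 and -0.30, against 0.00 with baseline adjustment.

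**How large might the imbalance be?** Assume a VAS SD of 25 mm, with 250 respondents in each cluster (2,250 and 750).
- Pain ICC 0.00174: SE = 25 × √(1.433 × (1/750 + 1/2250)) = 1.26 mm; 95% range ±2.47 mm.
- Pain ICC 0.02: design effect 1 + 249 × 0.02 = 5.98; SE = 2.58 mm; 95% range ±5.05 mm.

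At the edge of those ranges the change estimate moves by 1.24 to 2.53 mm at r = 0.5, and by 0.74 to 1.52 mm at r = 0.7.

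**Chronic pain.** If follow-up status is modelled without its baseline, the variance relative to a baseline-adjusted model is 1/(1-r²) on a linear-scale approximation: 1/(1-0.25) = 1.33 at r = 0.5 and 1/(1-0.49) = 1.96 at r = 0.7. These figures apply only under that reading of the text.

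**The case against.** The strongest reply is that the protocol already uses baseline pain: the outcome is a change, and the model carries ten covariates. That is right for VAS, and it would be wrong to call the VAS analysis unadjusted. But subtraction fixes the coefficient of baseline at 1, and the loss and the shift above are what remain. Self-rated health, age and BMI may carry some of the baseline-pain information, so the real gain could be smaller than the table shows.

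A second reply is that the sentence is shorthand. It also leaves out group allocation and the community random effect, which the comparison needs, and an analysis plan might say more. That is fair, but borrowing the remaining terms from the primary model would not clearly supply baseline VAS, because the primary model contains chronic pain status and not VAS.

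Three stronger readings are tempting, and the protocol does not support them.
- A reader might infer that the pain results will be biased. Over repeated randomisation the change score is unbiased. Respondents are a random sample of eligible residents, not people selected for high pain, so regression to the mean favours neither arm in advance.
- A reader might infer that chronic pain is compared at follow-up with no correction. The text speaks of changes; a model of both time points with a group-by-time term would use baseline. The protocol describes no such model, so the wording is undefined rather than wrong.
- A reader might infer that the activity-specific models adjust for the composite baseline. The text only says the approach is the same, and using each activity's own baseline is an equally natural reading.

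**Conclusion.** The point holds as a missing covariate in the named pain models. For VAS, the cost is an individual-level variance 1.18 to 1.43 times that of the baseline-adjusted model (SE about 8% to 20% larger) for an assumed r of 0.7 to 0.4, plus a conditional shift of 0.3 to 0.6 mm per mm of chance baseline imbalance. For chronic pain, the model needs defining; baseline pain is absent if the primary-analysis form is carried over.

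The sizes rest on assumed values of r, SD and pain ICC, on equal variances at both times, and on baseline VAS being weighed without the other covariates. A variance ratio does not convert directly into extra participants when the number of control communities is fixed at three. The primary analysis and its sample size are untouched. Change score and baseline adjustment are both valid estimators, and the second is more efficient, so this is a minor but worthwhile improvement.

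**What to change.** In section 7.2, state that:
- one-year low back VAS and knee VAS are each modelled with same-site baseline VAS as a fixed effect;
- one-year chronic low back pain and chronic knee pain are each modelled with same-site baseline chronic-pain status as a fixed effect, which also settles what change means for the binary outcome;
- the other listed covariates stay.

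For VAS the outcome may still be reported as a change: with baseline VAS in a linear model, the group coefficient is the same whether the outcome is follow-up or change.

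For the activity-specific outcomes, one sentence confirming that each model uses that activity's own baseline is enough.

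The cost is one covariate per model, from items already in the baseline questionnaire. The change should be fixed before outcome data are analysed, because section 5 says the analysts are not blinded to allocation.

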might be appropriate target groups when there are a number of segments competing for attention and resources. We placed special emphasis on the total number of persons in the segment (T), at risk status (R), and persuasibility (P) as segment priority factors. In the process of market (population) segmentation, we also adopted the stages of change model.[33] However, there were no data regarding the stages of change in physical activity behavior in this study population, so available behavioral data (i.e., walking times and engagement in stretching) was used to supplement the estimation of segment size. For promotion of aerobic activity, we selected a segment of women, 60–79 years of age, who currently have an interest in but are either not engaged in or are insufficiently engaged in regular walking behavior (less than 150 minutes/week), and who have low back or knee pain, regardless of severity. For flexibility and muscle-strengthening activities, we selected a segment of women, 60–79 years of age, who currently engage in flexibility and/or muscle-strengthening activities, either occasionally or daily, and who have low back or knee pain, regardless of severity. The estimated proportion of the target segment of the 40–79 aged population is 19% for aerobic activities and 16% for flexibility and muscle-strengthening activities, based on data from the Shimane Study in Unnan.[34] This targeting does not mean that our CWC ignores the physical activity in non-target people. Rather we aim that the CWC mainly affects the primary communication target with sophisticated messages and approaches and then it has a ripple effect on non-target people.

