## **7. Statistical analyses**

### *7.1. Sample size*

Based on available physical activity data for Unnan, the estimated rate of participation in regular aerobic, flexibility, and/or muscle-strengthening activities at baseline is 58% with an estimated intracluster (intraclass) correlation coefficient (ICC) of 0.00174. Groups A, FM, AFM, and the control group have equal sample sizes. The primary analysis is a comparison of the three intervention groups with the one control group. We obtained a sample size of 1,536 for the intervention groups and 512 for the control group, using the chi-square test by individual level, imbalanced [3 intervention; 1 control], a two-sided 5% significance level, and a power of 90% to detect an 8% difference in change in engagement in regular physical activity between the intervention and control groups (as described above in the social marketing section), without taking into account the design effect (DE) by the cluster randomization, as

follows:

$$n = \frac{\left( Z_{\alpha} \cdot \sqrt{(1+3) \cdot \frac{p_c + 3p_i}{1+3} \left( 1 - \frac{p_c + 3p_i}{1+3} \right)} + Z_{\beta} \cdot \sqrt{3 \cdot p_c(1-p_c) + p_i(1-p_i)} \right)^2}{3 \cdot (p_i - p_c)^2}$$

where

$p_i$  is rate of engagement in regular physical activity in intervention group

$p_c$  is rate of engagement in regular physical activity in control group

To retain power in the cluster randomized trials, the sample size should be multiplied by the DE, which is obtained as follows:[50]

$$DE = 1 + (\bar{m} - 1) \cdot ICC$$

where

$DE$  is design effect

$\bar{m}$  is the average cluster size

$ICC$  is intracluster (intraclass) correlation coefficient

If we plan to recruit an average of 500 participants in each cluster and assume a final sample of 250 in each cluster with a 50% response rate at baseline, the estimated DE is 1.44. The product of the obtained sample size of 512 in the control group and estimated DE of 1.44 is 738. Thus, recruiting nine clusters and 4,500 participants in the intervention groups and three clusters and 1,500 participants in the control group will retain expected statistical power. A total of 6,000 participants in the 12 clusters will be surveyed at baseline.

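### Exploratory subgroup analyses aim to detect differences in effect but name only stratification, which does not test a difference

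*Protocol*

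**What the plan says.** Section 7.2 labels these analyses exploratory: "As exploratory analyses, subgroup analyses will be conducted". The stated purpose and method are "subgroup analyses will be conducted to detect significant differences in intervention effect, after stratification by sex, age group". The two age bands meet at 60 years. A third factor sets the people whom the campaign chiefly addresses against everyone else: "the market segment (primary communication target segment and the remaining population". The closing paragraph of 7.2 sets one level for all analyses ("Significance will be set at" P < 0.05). The section lists the fixed effects of the primary generalized linear mixed model one by one, and none is a product of group with a subgroup factor. No interaction test is named elsewhere in the protocol.

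Section 4.1 describes two target segments, one for each kind of promoted activity. Their estimated share of the population aged 40–79 "is 19% for aerobic activities and 16% for flexibility and muscle-strengthening activities". The same section expects the campaign to act mainly on the target and to spread from there to other residents.

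**The concern.** A significant result in one stratum and a non-significant one in another does not show that the effects differ, because the two P-values also reflect how many people each stratum holds. The market-segment strata are very unequal, roughly 1:4 to 1:5, so the larger one is much likelier to reach significance even when the campaign works equally well in both. A reader shown an effect only outside the target segment could conclude that the targeting had failed when nothing but stratum size lay behind it. The same problem, in milder and symmetrical form, affects the splits by sex and age.

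**Working it through.** **Inputs.** Sections 4.1 and 7.1 give 58% v 66%, allocation 3:1, two-sided 5%, power 90%, ICC 0.00174 and 250 analysed per cluster. With three control and nine intervention clusters, that is 750 control and 2,250 intervention participants. Segment shares of 16% and 19% come from section 4.1.

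**The plan's own figure.** With a pooled rate of (0.58 + 3×0.66)/4 = 0.64, the formula in 7.1 gives 511.6, so 512 control and 1,536 intervention, as stated. DE = 1 + 249×0.00174 = 1.433 (stated 1.44), and 512×1.433 = 734 (stated 738). The inputs are confirmed apart from rounding.

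**Separate tests, same 8-point effect everywhere.** For a stratum holding share s:

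- m = 250s and DE = 1 + (m − 1)×0.00174
- SE² = DE × [0.58×0.42/(750s) + 0.66×0.34/(2,250s)]
- z = 0.08/SE and power = Φ(z − 1.96) + Φ(−z − 1.96)

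| Stratum | Control / intervention | DE | SE | z | Power |
|---|---|---|---|---|---|
| Target, 16% | 120 / 360 | 1.068 | 0.0532 | 1.50 | 32% |
| Remainder, 84% | 630 / 1,890 | 1.364 | 0.0263 | 3.05 | 86% |
| Target, 19% | 142.5 / 427.5 | 1.081 | 0.0491 | 1.63 | 37% |
| Remainder, 81% | 607.5 / 1,822.5 | 1.351 | 0.0266 | 3.01 | 85% |
| Half, 50% (assumed) | 375 / 1,125 | 1.216 | 0.0321 | 2.49 | 70% |

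Treating the strata as independent:

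- Significant only outside the target: 0.862×(1 − 0.324) = 58% for the 16% segment and 0.852×(1 − 0.370) = 54% for the 19% segment.
- Significant only inside the target: 0.324×0.138 = 4% and 0.370×0.148 = 5%.
- Equal halves, exactly one significant: 2×0.70×0.30 = 42%.

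On 8 degrees of freedom (12 clusters, less 3 density categories, less 1 for group), the two 'only outside' figures become 56% and 52%. For halves, power is 59% and the figure is 2×0.59×0.41 = 48%.

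Simulating 12 clusters with a cluster effect shared by both strata (40,000 runs) gave 51 to 57% for 'only outside'. For equal halves under z tests it gave 37%. A group-by-segment interaction test on the same simulated data rejected in about 5%, its nominal level.

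**Sensitivity of 'only outside' (uniform effect, normal tests, about 24 to 60% overall).**

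- 80% retention at follow-up: 54 to 58%.
- Segment baseline rate of 30 to 70% in place of 58%: 46 to 60%.
- Effects of 4.2, 6 and 9.4 points (4.2 and 9.4 are the median and upper end of the review cited in 4.1): 30 to 32%, 47 to 50% and 47 to 55%.
- Segment taken as the union of both definitions, at most 16 + 19 = 35%: 0.79×(1 − 0.57) = 34% at 8 points, 24% at 4.2 points and 26% at 9.4 points. With 8-df tests the 4.2-point case is 0.247×(1 − 0.167) = 21%.

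**Larger true effect in the target (19% segment, 8 points elsewhere).** At 12 points, power in the target is 69% and 'only outside' falls to 0.852×0.308 = 26%. At 16 points, power is 91% and it falls to 0.852×0.088 = 8%, below 'only inside' at 0.912×0.148 = 14%.

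**Power of the interaction test, 16 points in the target v 8 elsewhere.** If a cluster effect shared by both strata cancels, then for the 19% segment SE² = 0.58×0.42/142.5 + 0.74×0.26/427.5 + 0.58×0.42/607.5 + 0.66×0.34/1,822.5 = 0.00268. So SE = 0.0518, z = 0.08/0.0518 = 1.54 and power is 34%. For the 16% segment SE = 0.0554, z = 1.44 and power is 30%. Keeping each stratum's design effect in the sum lowers the 16% case to 28%.

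**The case against.** The strongest answer is that the protocol never says each stratum will be judged at P<0.05 and the verdicts set side by side. It states the aim as a difference in effect, and its P<0.05 is a general line. A statistical analysis plan that is not at hand might supply the test. This stands in part: the per-stratum rule is a likely reading, not the protocol's text, and a reader should not take it as a commitment. But the protocol does name a method for this aim, stratification, and that method alone does not deliver it.

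Two further inferences are tempting and not supported. One is that the plan depends on the segment contrast. It does not: the objective, the sample size and the primary test all cover everyone aged 40–79, section 4.1 says non-target residents are not ignored, and the subgroup work is exploratory. The other is that stratified testing would tend to show the reverse of the campaign's theory. That holds only if the effect is uniform, whereas section 4.1 expects it to fall mainly on the target. With a clearly larger target effect, the misleading pattern becomes uncommon.

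The figures also rest on simplifications. The 58% rate is applied to segments that are themselves defined by walking or exercise habits, the covariates in the model are ignored, and the 50:50 split is assumed because the protocol gives no distribution by sex or age. Finally, the interaction test has little power, so it will seldom settle the question. That is a reason to report its estimate and interval, not a reason to rely on paired P-values.

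**Conclusion.** The point holds as a mismatch between aim and method in an exploratory analysis. Stratification with a general P<0.05 does not test for a difference in effect, and no interaction is specified. If the strata were judged separately under a uniform 8-point effect, significance only outside the 16–19% segment would arise in about 51 to 58% of trials. The conclusion that the pattern would be common does not hang on one scenario: under uniform effects the range is about 24 to 60%. It does depend on uniformity, and on separate testing being what is done. For an assumed even split, exactly one half would be significant in about 37 to 48%. The primary and secondary analyses and their conclusions are untouched. The change is worth making because it is nearly free and prevents a likely misreading of how the targeting worked.

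**What to change.** Amend section 7.2 so that, for sex, age group and market segment in turn:

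- a group-by-subgroup interaction term is added to the primary mixed model, fitted to the full data;
- the interaction estimate is reported with its confidence interval;
- stratum-specific estimates and intervals are shown alongside, without separate claims of significance.

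Define the market segment from baseline data, identically in intervention and control communities. Section 4.1 gives two segments according to the activity promoted, section 7.2 refers to one, and the control communities receive no campaign that would decide between them.

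State that these analyses remain exploratory, that interaction power is low (about 30% even for a doubled effect in the target), and that a non-significant interaction is not evidence of equal effects.

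The cost is a few sentences and one extra model term per factor. No new data and no change to the sample size are needed.
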